## Abstract

**Background:**

Lumbar spine surgery is associated with significant postoperative pain and a high incidence of postoperative nausea and vomiting (PONV). Inflammation is a known contributor to PONV risk, and the neutrophil-to-lymphocyte ratio (NLR) is a cost-effective parameter for evaluating systemic inflammation. Erector spinae plane block (ESPB) under ultrasound guidance is a regional anesthesia technique that may reduce postoperative pain, inflammatory responses, and opioid consumption. However, evidence on the relationship between preoperative NLR, PONV, and the effects of ESPB is limited.

**Overview:**

This prospective, double-blind, single-center, parallel-group study will enroll 220 patients undergoing elective lumbar spine surgery under general anesthesia. Patients will be stratified by a preoperative NLR threshold of 2 into two equal groups and further randomized to receive either ultrasound-guided ESPB with ropivacaine or a saline control after anesthesia induction. All participants will receive standard PONV prophylaxis with intravenous ondansetron. Primary endpoints include the incidence of nausea, vomiting, and antiemetic requirements in the first and second 24-hour postoperative periods, as well as postoperative NLR. Secondary endpoints include pain scores, intraoperative anesthetic consumption, total postoperative analgesic use, time to first analgesic pump activation, patient satisfaction, recovery times, length of stay, opioid-related side effects, and serum neutrophil extracellular traps.

**Results:**

At the time of submission, the trial is ongoing and in the patient recruitment phase. No results are yet available.

**Discussion:**

The study is designed to evaluate whether preoperative NLR can serve as a biomarker for PONV and to determine the effect of ESPB on NLR, PONV, and postoperative recovery parameters in lumbar spine surgery patients. The findings may provide evidence for individualized PONV prevention strategies and the perioperative application of ESPB.

**Conclusion:**

This trial will clarify the predictive value of NLR for PONV and assess the efficacy of ESPB in modulating postoperative inflammation and improving recovery in lumbar spine surgery.

**Clinical trial registration:**

ClinicalTrials.gov identifier, NCT06127966.

## Highlights

This study employs rigorous screening criteria, a random allocation scheme, and a two-arm randomized controlled trial for four group.This study presents a rigorous method for comparing the preoperative neutrophil-to-lymphocyte ratio to PONV and the effect of erector spinae plane block on NLR and PONV in patients undergoing lumbar spine surgery.This study is conducted at a single center, and the findings may not apply to a broader population. A single-center design may limit the external generalizability of the findings. We plan to conduct future multicenter studies to validate the applicability and robustness of our results.

## Introduction

1

The incidence of lumbar spine disease significantly increases as the population ages and lifestyles change. The number of patients with lumbar spine disease in China exceeds 200 million, with lumbar disk herniation accounting for 15.2% of the total and showing a gradual upward trend over the years. Posterior lumbar fixation procedures are mainly indicated in patients with spinal instability or degenerative lumbar stenosis, rather than in those with simple lumbar disk herniation; however, spinal surgery often involves significant trauma and the use of high doses of opioids and anesthetics, resulting in a high incidence of complications such as severe postoperative pain and nausea and vomiting. If these complications are not effectively controlled, they can affect postoperative recovery and extend the length of hospital stay.

Postoperative nausea and vomiting (PONV) are common complications (17–20). In patients undergoing lumbar surgery, PONV can lead to further complications. The most common consequence is an extended hospital stay. More severe complications can include implant displacement, aspiration, pulmonary infection, and spinal cord injury (1–3). Although PONV is generally self-limiting and nonfatal, it significantly increases the risk of dehydration, electrolyte imbalance, suture line rupture, hypertension, bleeding, esophageal rupture, and life-threatening airway obstruction. PONV can prolong post-anesthesia care unit (PACU) stay and overall hospitalization time, decrease patient satisfaction, lead to unexpected readmissions, and increase hospital costs. Therefore, preventing and managing PONV are crucial for improving patient outcomes and reducing healthcare costs (4).

The first step in PONV prevention is identifying risk factors and high-risk patient groups. Many anesthesia-related risk factors contribute to PONV, including anesthesia techniques, volatile anesthetics use, nitrous oxide use, anesthesia duration, opioid use, and surgery type (5). Inflammation increases the risk of PONV; the neutrophil-to-lymphocyte ratio (NLR) (21, 22) is a cost-effective parameter for diagnosing and monitoring systemic inflammatory diseases (6, 7). Severe vomiting during pregnancy is related to NLR, but research exploring the potential relationship between PONV and NLR is limited. Although PONV prevention increases healthcare costs, it costs less than treating PONV and the associated complications. Therefore, establishing evidence-based parameters for identifying patients who require preoperative PONV prevention is important for reducing hospital costs.

Lumbar spine surgery is a painful surgical procedure. Postoperative pain is classified as acute primarily because of the physiological stress response triggered by surgical trauma and inflammation. Ultrasound-guided erector spinae plane block (ESPB) is a new local anesthetic technique that blocks the dorsal and ventral branches of the thoracolumbar spinal nerves. It is used in thoracic, abdominal, breast, urological, weight loss, and hip joint surgeries for combined anesthesia and postoperative pain control. Under ultrasound guidance, ESPB provides precise localization, accurate drug administration, effective pain relief, and a minimal effect on the patient’s overall condition, with no apparent adverse reactions (8–13). However, its application in lumbar spine surgery is limited. Reports suggest this technique can also be used in lumbar spine surgery.

Performing ESPB during lumbar–sacral surgery significantly reduces postoperative pain scores, decreases patient stress responses, lowers inflammatory reactions, and reduces the dosage of opioid medications and their immunosuppressive and other side effects (8–13). Inflammatory mediators may influence the nausea and vomiting center by entering the circulation. Neutrophils are key effectors of sterile inflammation; increased and activated neutrophils form neutrophil extracellular traps (NETs) after acute trauma. NETs are involved in the response to various infectious and non-infectious stimuli. Following surgical trauma, increased NET formation may amplify systemic inflammatory responses and promote the release of proinflammatory cytokines. These mediators can sensitize the chemoreceptor trigger zone (CTZ) and the vomiting center in the brainstem, thereby increasing the risk of PONV. Ultrasound-guided erector spinae plane block (ESPB) may attenuate this inflammatory cascade through sympathetic blockade and reduction of nociceptive inputs. By decreasing the surgical stress response, ESPB could lower neutrophil activation and consequent NET formation, thereby modulating postoperative inflammatory burden. However, reports on whether ESPB affects NLR, NETs, and PONV are limited.

Therefore, this study aims to investigate whether preoperative NLR is a biomarker for PONV and explore the effect of ESPB on NLR and PONV.

### Objective

1.1

The primary objective of this study is to investigate the effects of ESPB on NLR and PONV. The secondary objectives are to explore whether preoperative NLR can serve as a biomarker for PONV and to examine the analgesic effects of ESPB in spinal surgery and its influence on opioid medication dosage.

## Methods and analysis

2

### Study design

2.1

This prospective, single-center, double-blind, randomized controlled study was conducted at the First Affiliated Hospital of Shandong First Medical University, a tertiary university hospital in China. The study is registered with ClinicalTrials.gov (NCT06127966) and is scheduled to commence on November 1, 2023, with an expected completion time of 2 years. The study protocol adhered to the Intervention Trial Recommendation Statement and Uniform Standard Statement for Reporting Trials to ensure accurate reporting of trial results. We used the SPIRIT reporting guidelines (14).

### Study setting

2.2

This study was performed at The First Affiliated Hospital of Shandong First Medical University in Jinan City, Shandong Province.

### Patients and recruitment

2.3

The study will include 220 patients aged 18–80 years, classified as American Society of Anesthesiologists (ASA) grade I to III planning to undergo elective prone lumbar spine surgery under general anesthesia from August 1, 2025, to September 1, 2026. Each patient will provide written informed consent and be assigned randomly to a different group based on the inclusion and exclusion criteria. All patients participating in the trial were given 3 to 5 days to learn about the study before signing the informed consent form. Preoperatively, the NLR was calculated by dividing the neutrophil count by the lymphocyte count in the complete blood count. A preoperative NLR threshold value of 2 (23–29) was accepted; the patients were divided into two groups based on values above and below 2; each group comprised 110 patients. Patients with a preoperative NLR < 2 are included in Group A (*n* = 110); those with a preoperative NLR > 2 are included in Group B (*n* = 110). Using a random number table, Group A is divided into an ESPB (EA group, *n* = 55) and a control group (CA group, *n* = 55); Group B is divided into an ESPB (EB group, *n* = 55) and a control group (CB group, *n* = 55). Randomization is achieved using a computer-generated table of random numbers (Figure 1).

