### Data collection and management

2.7

Demographic and clinical data will be collected from all patients, including age, sex, height, weight, body mass index, ASA classification, surgery duration, the intraoperative consumption of drugs, such as propofol and remifentanil, and total analgesic consumption in the first and second 24-h periods postoperatively. Nausea, vomiting, and antiemetic requirements will be recorded in the PACU for the first and second 24-h periods postoperatively. The VAS scores will be recorded at rest and during movement at 2, 4, 6, 8, 12, 24, and 48 h postoperatively. The time of the first pressing of the analgesic pump will be documented. The rescue analgesia rate and analgesic satisfaction scores will be assessed at 24 and 48 h postoperatively. Postoperative satisfaction will be evaluated (0 = dissatisfied, 1 = average, 2 = satisfied, and 3 = very satisfied). Postoperative awakening and extubation time will be recorded. The extubation criteria are that the patient resumes spontaneous breathing with a tidal volume ≥7 mL/kg, demonstrates swallowing reflex, and can follow instructions, maintaining SpO_2_ above 90%. The duration of the postoperative PACU stay and discharge time will be recorded. The occurrence rates of opioid-related side effects will be recorded, including dizziness and urinary retention. The serum NET levels will be measured. In this study, we will assess NETs levels indirectly by quantifying cell-free double-stranded DNA (cf-dsDNA) in serum using the PicoGreen dsDNA quantitation method. Serum samples (5 mL) are collected, centrifuged, and stored at −20 °C. The working dye solution is prepared by diluting PicoGreen reagent 1:200 in TE buffer. A standard curve is constructed using serial dilutions of calf thymus DNA. Equal volumes of diluted sample and dye are mixed and incubated in the dark at room temperature for 5 min. Fluorescence intensity is measured using a fluorescence microplate reader, and the cf-dsDNA concentration (ng/mL) is calculated using the standard curve. This measurement serves as an indirect indicator of NET formation in the postoperative period.

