### Sample size calculation

2.11

To calculate the sample size for the primary research objective, use the “Tests for Two Ordered Categorical Variables” module in PASS software. Set the test power to 1 − β = 0.8 and significance level *α* = 0.05; use a 1:1 ratio between the NLR < 2 and NLR ≥ 2 groups. For the NLR < 2 group, the composition ratios of the PONV states considered as no, nausea, retching, and vomiting are 0.575, 0.050, 0.001, and 0.375, respectively. For the NLR ≥ 2 group, the composition ratios for PONV no, nausea, retching, and vomiting are 0.250, 0.100, 0.050, and 0.600, respectively. The calculated sample size is 94 cases, considering a 10% dropout rate. The final sample size is 106, with 53 patients in each group.

Use the “Tests for Two Proportions” module in PASS software to calculate the sample size for one of the secondary objectives: determining whether preoperative NLR can serve as a biomarker for PONV. Set the test power to 1 − β = 0.8 and significance level to *α* = 0.05; use a 1:1 ratio between the control and thoracic paravertebral nerve block groups. Nausea and vomiting rates are 8.3 and 33.3%, respectively. The calculated sample size is 82, considering a 10% dropout rate. The final sample size is 92, with 46 patients in each group.

The baseline NLR levels are first divided into two strata, and randomization is performed within each stratum. The sample size of each group in this study is 55.

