### Statistical analysis

2.13

All data will be statistically analyzed using SPSS software (version 25.0). Continuous variables such as VAS scores will be represented by the mean ± standard deviation if they follow a normal distribution. An independent sample t-test will be employed to compare intergroup differences. If the data do not conform to a normal distribution, the Wilcoxon rank-sum test will be used to compare groups.

For categorical variables, such as sex, the chi-squared or Fisher’s exact test will be used to assess intergroup differences. For ordinal data, such as the degree of vomiting, the Wilcoxon rank-sum test will be used for between-group comparisons.

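### The NLR biomarker question is planned around an unadjusted comparison of two non-randomised groups cut at 2, which is open to modest confounding and measures neither discrimination nor added value

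*Protocol article*

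**What the plan says.** The Objective section (1.1) makes the biomarker question secondary: "The secondary objectives are to explore whether preoperative NLR can serve as a biomarker for PONV". The abstract's conclusion is firmer: "This trial will clarify the predictive value of NLR for PONV".

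Section 2.3 forms the groups: "the patients were divided into two groups based on values above and below 2", with 110 patients in each. Each is then split 55:55 between ESPB and saline. Section 2.11 confirms the order: "The baseline NLR levels are first divided into two strata, and randomization is performed within each stratum".

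Section 2.11 also contains a calculation comparing NLR < 2 with NLR ≥ 2 on a four-level PONV grade. It is labelled as serving the primary objective. The calculation labelled as serving the biomarker objective compares block with control. By content, the NLR calculation is the one that bears on the biomarker question.

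Section 2.13 lists t, Wilcoxon, chi-squared and Fisher tests. For ordinal data such as vomiting grade, "the Wilcoxon rank-sum test will be used for between-group comparisons". It names no regression, stratified test, analysis of NLR as a continuous value, or measure of discrimination. Section 2.7 lists candidate covariates, which get no analytic role: "Demographic and clinical data will be collected from all patients, including age, sex, height, weight, body mass index, ASA classification, surgery duration".

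**The concern.** Randomisation protects the ESPB comparison but not the comparison of low with high NLR. Nothing in the design balances age, sex, ASA class or surgery duration between those groups. The introduction itself counts anaesthesia duration, opioid use and type of surgery among the risk factors for PONV, and section 2.4 admits procedures from discectomy to two-level fusion. A difference between NLR groups could therefore partly reflect case mix, and a real but weak association could be hidden by it.

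The chosen summary also does not match the claim. A group p-value at one cut says that two distributions differ. It does not say how well NLR separates patients who will have PONV from those who will not, or whether it adds to what is already known before surgery. It takes the cut of 2 as given. At stake is a claim meant to support individualised prevention.

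**Working it through.** **1. The plan's own figure (section 2.11).** Inputs: NLR < 2 proportions 0.575, 0.050, 0.001, 0.375 (they sum to 1.001 and are rescaled); NLR ≥ 2 proportions 0.250, 0.100, 0.050, 0.600; power 0.80; α 0.05, taken as two-sided.

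- Probability that a high-NLR patient has the worse grade, ties counted half: P = 0.6506.
- Tie-corrected rank-sum formula: N = (1.960 + 0.842)² × (1 − Σp̄³) / [12 × 0.25 × (P − 0.5)²], where p̄ is the mean proportion per grade.
- Result: N = 93.9, so 94, or 47 per group. 47/0.9 = 52.2, so 53 per group and 106 in total.

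Both stated figures reproduce with an unadjusted Wilcoxon test at the cut of 2. Section 2.13 names the same test for vomiting grade.

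**2. Planned size of the contrast.** Any PONV is 1 − 0.575 = 42.5% against 1 − 0.250 = 75%. That is 32.5 points, with odds ratio (0.75/0.25)/(0.425/0.575) = 4.06.

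**3. What confounding could add (assumed inputs).** Spurious difference = imbalance × risk difference due to the factor, with 45% baseline risk.

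- Odds ratio 2.5: the risk becomes 67.2%. A 20-point imbalance gives 0.20 × (67.2 − 45) = 4.4 points.
- Odds ratio 2: the risk becomes 62.1%. A 10-point imbalance gives 0.10 × (62.1 − 45) = 1.7 points.

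A second illustration assumes no NLR effect, 25% PONV in men and 110 patients per NLR group. With a sex odds ratio of 3 the risk in women is 50%. Female shares of 40% and 60% then give 35% and 40% PONV, an apparent NLR odds ratio of 1.24.

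| Sex odds ratio | Imbalance (points) | Apparent NLR odds ratio | Chance of significance in that direction (nominal 2.5%) |
|---|---|---|---|
| 2 | 10 / 20 / 30 | 1.07 / 1.15 / 1.23 | 4% / 7% / 11% |
| 3 | 10 / 20 / 30 | 1.11 / 1.24 / 1.38 | 6% / 12% / 21% |

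**4. ESPB.** Use the block-calculation rates of 8.3% and 33.3%. With 55:55 in both strata and no NLR effect, each NLR group expects (8.3 + 33.3)/2 = 20.8%, so there is no confounding. If the block worked only at NLR < 2, the pooled rates would be 20.8% and 33.3% although NLR made no difference in control patients. With 110 per group that contrast would be significant about 55% of the time.

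**5. Dichotomising.** For a normal marker with a linear effect, a split at the median keeps 2/π = 64% of the information, and a 30:70 split keeps 58%. After 10% dropout, 220 × 0.9 = 198 patients; 198 × 0.637 ≈ 126.

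**6. Is adjustment affordable?** With 99 evaluable per NLR group and the plan's rates, unadjusted power for any PONV is 99.8%. Replacing n by n(1 − R²), with covariates explaining an assumed 10%, 20% or 30% of NLR-group variance, gives 99.5%, 99.0% and 97.9%. In control patients only (about 49.5 per group) power is 92% unadjusted and 89%, 85% and 80% under the same assumptions.

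**The case against.** The strongest reply is that section 2.13 is a short list of tests by data type in a journal article. It does not say which analysis answers the biomarker question, and a plan not shown may contain a model. Forming strata at 2 for randomisation does not bind the analysis to a binary NLR. This is fair as far as it goes: the link is inferred. But the point does not rest on silence alone. The sample size is a two-group rank test at the cut of 2, and the same test is named in the analysis section.

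A second reply is that a predictor need not be causal, so NLR may predict PONV even if it partly tracks age or sex. That is right, and confounding should not be the whole charge. Adjustment matters because it shows what NLR adds to known factors. Even for pure prediction, a group p-value gives no discrimination.

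Third, the biases in steps 3 and 5 rest on assumed inputs and are small beside the planned contrast. This also stands.

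Stronger readings that a reader might infer are not supported:
- ESPB as a confounder: it is randomised equally within each stratum, so only interaction (or, slightly, very unequal dropout) matters.
- Dichotomising as a loss of most of the information: about 36% is lost under the stated assumptions.
- Confounding as a full explanation of the expected effect: apparent odds ratios of 1.07 to 1.38 are far from 4.06.

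**Conclusion.** The point holds in limited form. The biomarker objective is planned around an unadjusted contrast of non-randomised groups at one cut. That design can inflate or mask a weak association and cannot, on its own, support a statement about predictive value. The size is modest: about 1.7 to 4.4 points of spurious difference for one factor (assumed odds ratios 2 to 2.5, imbalances 10 to 20 points, baseline 45%) against a planned 32.5. About 36% of the information is lost if log NLR is normal, its effect is linear and the cut lies near the median. The case for changing the plan is that a better analysis uses data already collected and costs almost nothing. The sample size and the randomised ESPB comparison are not put in doubt by this point.

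**What to change.** In section 2.13, state the biomarker analysis separately:

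- Logistic regression of PONV (or proportional odds for the 0–3 score) on continuous log NLR, with age, sex, BMI, ASA class, surgery duration, ESPB arm and an NLR-by-ESPB term. Results shown also in control patients may replace the interaction term.
- The adjusted odds ratio with 95% CI, and the AUC with and without NLR. Surgery duration is known only afterwards, so give the AUC comparison without it too if preoperative use is intended.
- A note that the fixed 110:110 quota means predictive values do not reflect the natural distribution of NLR.
- NLR < 2 versus ≥ 2 by the planned test, kept as supportive.

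The cost is wording and a little more analysis; recruitment is still under way and the wording can be settled before unblinding. The unadjusted difference may shrink. At the NLR calculation's rates about 198 × (0.425 + 0.75)/2 = 116 patients have PONV, which carries eight terms comfortably. At 20.8% there would be about 41, and the covariate list should then be shortened by a rule fixed in advance. New baseline questions on smoking or previous PONV are not required: asked only of later patients, they could not serve as whole-trial covariates.

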**Figure 1 fig1:**
[figure not shown]
Study flow chart.

### Inclusion criteria

2.4

The inclusion criteria are patients aged 18–80 years scheduled for elective prone lumbar spine surgery under general anesthesia, specifically including one- or two-level posterior lumbar decompression, discectomy, or posterior lumbar interbody fusion (PLIF) for degenerative conditions. These patients must have an ASA classification of grade I to III and sign informed consent forms to participate in this clinical study.

### Exclusion criteria

2.5

The exclusion criteria include preoperative blood transfusion, uncontrolled systemic diseases, patients with known uncontrolled systemic inflammatory diseases (e.g., rheumatoid arthritis, lupus, or active infections), gastrointestinal system disorders, history of antiemetic (15) and anticholinergic drug use, history of adverse reactions related to surgery, deformity correction surgeries, defined as procedures involving instrumentation across three or more levels or aimed at correcting scoliosis or kyphosis, infection at the puncture site, coagulation disorders, long-term use of sedatives and analgesics before surgery, psychiatric disorders, language communication barriers, allergy to ropivacaine, involvement in other clinical studies in the last 3 months, history of previous lumbar surgery, and unwillingness to participate in this study.

